## **5. Hypothesis**

We hypothesize that smokers who receive the EMA-based smoking cessation intervention will have higher scores in Incremental Behavior Change towards Smoking Cessation (IBC-S), which measures the behavioral progression towards smoking cessation, and higher biochemically validated abstinence than those who do not receive the intervention at 3-month follow-up.

## **6. Study design**

The proposed study comprises a 2-arm (allocation ratio 1:1) pragmatic RCT to assess the efficacy of the EMA-based smoking cessation intervention and the EMA-based observational study. Throughout the 7-day participation, all recruited participants will complete an EoD survey and 4 time-based system-triggered EMA each day. The surveys will be prompted by a smartphone application (app) installed in their own mobile phones. The prompting time will be personalized and pre-scheduled by the participants. The information collected in the app will be used to develop an EMA-based intervention including a quit plan and 10-week quitting reminders and for an EMA-based observational study. I will randomly allocate half of the participants (intervention group) to receive the EMA-based intervention. All participants will then be contacted for a follow-up at 3-month and 6-month.

## **7. Subjects**

This proposed study aims to recruit daily tobacco users, regardless of intention to quit. We shall send mass emails to the University of Hong Kong (HKU) staff and students, post recruitment advertisements in media and smoking cessation clinics, or actively invite smokers at outdoor smoking hotspots to participate. Outdoor smoking hotspots (i.e., urban places with a butt

collector and a cluster of smokers) were shown as feasible platforms for efficient smokers' recruitment (21). The inclusion criteria are: (1) daily consumption of tobacco products (including traditional cigarettes, electronic cigarettes, and heated tobacco products) in the past week; (2) age  $\geq 18$  years; (3) owning a mobile smartphone with internet access; (4) staying in Hong Kong during the 1-week EMA study period; and (5) able to read and write Chinese. To confirm the smoking status of the participants, exhaled carbon monoxide will be measured and required to be 4ppm or above, or saliva cotinine to be 30ng/ml or above. Because the proposed study aims to promote smoking cessation in smokers who do not plan to use smoking cessation aids, we will exclude smokers who (1) plan to use smoking cessation services or medication in the coming month or (2) using smoking cessation services, or using nicotine replacement therapy in the past 7 days. Smokers who reported having mental illnesses and female smokers who are pregnant are also excluded as they need more specific smoking cessation intervention.

To date, there have been no randomized controlled trial (RCT) to provide an estimate of effect size for the EMA-based intervention. Our team's previous RCT of testing a personalized smoking cessation intervention showed that the effect size (risk ratio) can be as high as 1.68 (22). Our current outreach health promotion (funded by Health Care Promotion Scheme, project no. 01170418) showed that each month we can recruit 30 to 60 smokers to participate in the smoking cessation RCT. Considering the limited study period covered in this funding application, this proposed study targets to recruit 440 smokers in 11 months.

## **8. Recruitment procedures**

In the outdoor recruitment sessions, the recruitment staff will approach and distribute souvenirs (e.g., a tissue pack) or leaflets to the smokers at outdoor smoking hotspots for 3-4 hours in daytime. If a smoker is willing to accept them and talk to the recruitment staff, the staff will advise the smoker to quit using the AWARD protocol and ask further questions related to eligibility. The AWARD protocol includes (1) **A**sk the smoking history, (2) **W**arn about the high risk (i.e., half of the smokers will die of smoking-related diseases), (3) **A**dvice to quit, (4) Introduce smoking cessation services and medications (**R**efer), and (5) Repeat the above advice (**D**o-it-again) (23). Our previous studies have shown that the AWARD protocol is a feasible and appropriate tool used by non-healthcare professionals to promote smoking cessation.

The promotion sessions will be organized at outdoor smoking hotspots, which will be selected from the public places in our funded project of Health Care Promotion Scheme (Project number 01170418). These locations cover New Territories, Kowloon, and Hong Kong Island, and the feasibility study supports that the number of subjects recruited in these locations will be higher than that in other places. Thus, they will be used in this study. Pre-promotion site visits and replacement of hotspots with reduced number of smokers will be done to ensure that the maximum number of smokers can be approached.

Eligible participants will be given more details of the study, and asked to consent to participation via an online form on Qualtrics. Then, the staff will assist the participants to install the EMA app on their mobile phones. Participants will need to complete a simple baseline questionnaire, which documents sociodemographic characteristics, smoking cues, smoking behaviours and contact information. Afterwards, the staff will ask the participants to select 7 consecutive days as the study period. Participants will be asked to set up the time they would like to receive the first time-based EMA from 6:00 am to 12:00 nn to undertake the regularly prompting EMA. For example, if a participant set the first prompt time at 9:00 am, he will be asked to complete an EMA survey at 9:00 am, 12:00 nn, 3:00 pm, 6:00 pm and an EoD survey at 9:00 pm. Then the staff will set up the EMA schedule in the app for the participants.

Because the recruitment time for each participant at outdoor hotspots is always limited, recruitment procedures will be brief. Participants need not set up the EMA schedule with the app at recruitment. Instead, the staff will document the EMA schedule and proceed with the set-up procedures in the back-end after the recruitment session. A pocket-sized card including the EMA schedule and instruction of using the app will be provided onsite.

Some participants will know the study from publicity emails or advertisement. If they are interested, they can complete an online application form (using Qualtrics or Google form). Recruitment staff will make appointment with the interested participants to complete the recruitment procedures.

Our recruitment staff will provide virtual recruitment procedures for those potential participants who don't like to have face-to-face recruitment procedures. First, the recruitment staff will contact those participants and delivery a cotinine saliva test device to the potential participants. Then the recruitment staff will have a virtual meeting with the potential participants after they receive the cotinine saliva test device. During the virtual meeting, our recruitment staff will guide the potential participants to validate their cotinine level, then assist eligible participants in completing the baseline questionnaire, and install and set the EMA app.

## **9. Randomization and allocation concealment**

Simple individual randomization (1:1 allocation ratio) will be applied. Qualtrics' randomizer will be used for random allocation. This will be implemented by a research staff, who is not involved in the recruitment, so that all recruitment staff and participants will be concealed to the group allocation at recruitment. After a participant consent to the trial, our research staff will access the randomizer in Qualtrics and enter the individual participant's 5-digit identifier. With the randomizer feature in place, Qualtrics will display a page indicating either the intervention group or the control group. A separate Qualtrics account for the randomizer will be used, and group allocation will be separated from research data. Information of the participants in the intervention group will be transferred to the research nurse for the EMA-based intervention.

## **10. Blinding**

Participants will not be blinded to the intervention. Assessors of the follow-up outcomes and the research investigators will not be involved in the recruitment and intervention delivery and will be blinded to the group allocation (single-blinded design).

## **11. Intervention**

***Smartphone application*** A EMA app will be developed to facilitate documentation of all smoking cues and smoking-related behaviors. After each recruitment, the staff will set up all EMA schedules of the participants in the back-end. Participants can then receive the EMA prompts and complete the EMAs. Participants will use the last 5 digits of their mobile phone numbers as identifier. They will use the app to complete an EoD survey and 4 time-based EMA each day in the 7 consecutive study days.

In each time-based EMA time window, the app will firstly prompt the user to answer questions on the smoking cues, smoking behaviours, and the association between smoking cues and smoking-related behavior, which only takes about 1 minute. If the user does not respond to an EMA prompt, 2 subsequent prompts will be generated. If these additional prompts are not responded to, the EMA will regard nonresponse as missing data. All data will be uploaded to our server immediately after each EMA completion.

The EMA questions on smoking cues cover 3 domains: mood, sleep, environmental triggers. The mood domain includes (1) irritable, depressed, restless, tension, stress, and other emotional cues related to smoking; Sleep domain includes insomnia symptoms for the last night. Environmental triggers include (1) social gathering; (2) family/friends/partner smoking; receive tobacco products/encouragement from others; (3) any other environmental smoking cues. Smoking-related behaviors include (1) nicotine craving (2) whether he/she has bought/consumed tobacco (traditional cigarettes, heated tobacco products and electronic cigarettes) in the past 3 hours (yes/no), (3) whether the tobacco consumption has been due to the exposure to the pro-smoking cues, and (4) other reasons of tobacco consumption (e.g., kill time, habit, leaving a place where smoking is not allowed). EoD survey includes (1) daily tobacco consumption; (2) time to consume the first cigarette after waking; (3) all EMA questions; (4) tobacco control policy questions which include daily exposure to health warnings on their tobacco pack/POS tobacco display/exposure to hotspot.

Participants will be encouraged to improve compliance via WhatsApp reminders if their compliance rate drops to 50% or below in the first 3 study days. To increase uptake and compensate the time spent by the participants, a small amount of cash incentive is needed. All participants will be given a HK\$50 gift voucher for the completion of baseline survey. They will be rewarded a HK\$ 15 gift voucher for completing 3 time-based EMA surveys within each day. They will be further rewarded a HK\$ 10 gift voucher for completing all surveys in each day. In addition, participants will be further rewarded HK\$ 25 gift voucher for completing more than 80% of 7 days time-based EMA surveys. Participants who complete biochemical validation at 3 months or 6 months follow up will obtain an additional HK\$50 gift voucher.

**EMA-based intervention** Based on the EMA of each participant, a trained research nurse will review their (1) nicotine dependence; (2) intensity and frequency of reported cravings; and (3) the impact of exposure to pro-smoking cues on smoking behaviors. A personalized quit plan will be developed based on tailored suggestions from the US clinical practice guideline for smoking cessation, Smoking Cessation, Smoking Cessation Information Kit (published by Department of Health), the theory of Health Action Process Approach, and the self-determination theory. Our recent studies showed that interventions based on these theories are effective (22, 24). Half of the randomly selected participants (intervention group) will receive this quit plan via a nurse-led phone call, email, and WhatsApp. The nurse will then design a quit plan including (1) self-help techniques on handling craving; (2) suggestions to avoid the reported pro-smoking cues; (3) whether to quit progressively or abruptly; (4) referral for existing smoking cessation service; and (5) instruction of using over-the-counter (OTC) nicotine replacement therapy (NRT), if OTC-NRT is preferred by the participant. Participants will then receive tailored quitting reminders via instant messaging social media (i.e., WhatsApp, WeChat) and voluntarily discuss their quit plan with the nurse in the subsequent 10 weeks.

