### 2. Aims

(1) To evaluate the feasibility and efficacy of EMA-based smoking cessation intervention for smoking cessation

(2) To analyze the association between smoking cues and smoking-related behaviors in the local context. Smoking cues include exposure to POS tobacco displays, health warnings, scenes of others' smoking, alcohol use, social gathering, media items on promoting smoking cessation, feeling stressed/depressed, and other smoking-related cues. Smoking-related behaviors include purchase of tobacco, tobacco consumption, and nicotine craving.

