Three types of EMA have been commonly used for tobacco research (12). First, “event-contingent” assessment is used to yield data triggered by an event of interest and can be either initiated by subjects or automatically documented by sensors (e.g., Global Positioning System [GPS]). However, achieving high compliance of subject-initiated EMA is difficult as it relies on participants to actively input data and may pose large burden to the participants. Meanwhile, the accuracy of sensor-based EMA such as wristbands to recognize smoking and GPS is still emerging. The second type of EMA is “signal-contingent/time-based” assessment, which requires subjects to pre-schedule assessments at certain times or at random time in scheduled time blocks. The last type of EMA is to complete one retrospective assessment on previous behaviors and attitude at one particular time of a day (e.g., end-of-day [EoD] survey before night sleep). Time-based EMA and EoD survey will be applied in this proposed research because these assessments minimize subjects’ burden and time, and the cost of instrument development is

lower.

EMA is a valid measurement tool to understand smokers' nicotine craving (15, 16) and environmental cues (17, 18). Measurements at different time points help clarify temporal and causal relationship between event exposures and smoking-related outcomes (12). For instance, EMA studies have revealed how nicotine craving is precipitated by internal stimuli like stress, depressed mood, negative affect, and pain. Another major research direction is to examine the effect of contextual factors on purchase and consumption of tobacco, such as tobacco marketing, health warnings, and alcohol use, using EMA data. Hence, the findings from EMA should have greater impacts on policy implementation than previous retrospective and cross-sectional studies.

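### Aim 2 names alcohol use and smoking-cessation media as cues to be analysed, but the described EMA and end-of-day content has no dedicated item for either

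*Protocol*

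**What the plan says.** Section 2 (Aims) sets out, as Aim 2, an analysis of the association between smoking cues and smoking-related behaviours. It starts the list of cues with point-of-sale displays, health warnings and scenes of others smoking, and continues with "alcohol use, social gathering, media items on promoting smoking cessation, feeling stressed/depressed, and other smoking-related cues".

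Section 11 (Intervention, smartphone application) describes what will be asked. It opens with a general scope: "A EMA app will be developed to facilitate documentation of all smoking cues and smoking-related behaviors". It then narrows this: "The EMA questions on smoking cues cover 3 domains: mood, sleep, environmental triggers". Mood covers irritability, depression, tension, stress and similar states. Sleep covers insomnia symptoms the night before. Environmental triggers begin with social gathering, go on to smoking by family, friends or partner, and end with "receive tobacco products/encouragement from others; (3) any other environmental smoking cues". The end-of-day survey asks about daily consumption and time to first cigarette, repeats all the EMA questions, and adds "tobacco control policy questions which include daily exposure to health warnings on their tobacco pack/POS tobacco display/exposure to hotspot".

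Section 14 (Statistical analysis) recodes checklist options into binary variables. It then relates cues to behaviours by GEE, or by a linear mixed model when the outcome is not binary.

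**The concern.** An association can be estimated only for an exposure that is recorded as present or absent on each occasion. Aim 2 commits the study to alcohol use and cessation media by name, yet the content description does not show where either would be recorded. If the app is built from Section 11 as written, the part of Aim 2 that concerns these two cues would rest on whatever respondents happen to enter under a residual category. The choice of items is fixed when the data are collected, so no later analysis plan could supply an exposure that was not asked about.

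**Working it through.** The protocol states no figure on this point. The check is to match each cue named in Section 2 to the content described in Section 11.

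| Cue named in Aim 2 | Named item in Section 11 |
|---|---|
| Point-of-sale displays | Yes, end-of-day survey |
| Health warnings | Yes, end-of-day survey |
| Others' smoking | Yes, EMA and end-of-day |
| Alcohol use | None |
| Social gathering | Yes, EMA and end-of-day |
| Media promoting cessation | None |
| Stressed or depressed | Yes, EMA and end-of-day |

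Named cues: 7. With a named item: 5. Without: 7 − 5 = 2, that is 2/7 or about 29%. The residual class of other cues in Aim 2 corresponds to the catch-all in Section 11 and is not counted.

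Two other places might supply the missing exposures.

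- **The catch-all.** It does not ask about any particular cue. A respondent who drank but did not think of drinking as a smoking cue leaves it blank, and so does one who did not drink. With a named option in a check-all-that-apply list, an unticked box answers a question about that cue and can be coded as no. With the catch-all, the same blank mixes the unexposed with the unprompted. For cessation media the problem is greater: the message discourages smoking, so few respondents would think to list it as a smoking cue.
- **The baseline questionnaire.** According to Section 8 it is a simple form "which documents sociodemographic characteristics, smoking cues, smoking behaviours and contact information". Its cue content is not itemised and it is completed once, so it cannot give the repeated, time-specific exposure that an EMA analysis needs.

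**The case against.** The strongest reply is that Section 11 is a summary and not the questionnaire. Its lists are introduced as inclusions, the app is still to be developed, the stated scope is all smoking cues, and the catch-all leaves room for alcohol. This reply stands to the following extent. A reader might infer that there will be no exposure data at all for the two cues, or that Aim 2 is unanswerable for them. The document does not support that. Some alcohol reports may reach the catch-all, and how its entries are captured (free text, sub-options or a single box) is not stated. But Section 11 describes content down to individual reasons for smoking and adds sleep and hotspot exposure, which Aim 2 does not name. A general statement of scope does not create a prompt for a cue that the detailed list leaves out.

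Other tempting inferences also go too far:

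- The checklist in Section 14 omits both cues, but it is only an example. It omits social gathering too, which Section 11 does list, so it proves nothing about the survey.
- Section 4 mentions contextual factors "such as tobacco marketing, health warnings, and alcohol use, using EMA data", but there it describes a research direction in EMA work generally. The commitment to measure alcohol comes from Aim 2.
- One might argue that alcohol confounds the social-gathering association and must be adjusted for. Gathering may equally lead to drinking and drinking to smoking, which would make alcohol a mediator. Within one 3-hour window the order cannot be settled, and Aim 2 promises no alcohol-adjusted effect.
- The number of scheduled surveys, 440 × 7 × (4 + 1) = 15,400, is a ceiling at full recruitment and full response. The two pilots reached 48% and 73.5% of prompts. The figure measures survey volume, not harm.

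**Conclusion.** The mismatch is real and limited. Two of the seven cues named in Aim 2, alcohol use and cessation media, have no dedicated item in the described EMA or end-of-day content. As the plan is written they cannot be dependably analysed in the GEE. The gap is firmer for cessation media than for alcohol, which might partly be recovered from the catch-all. The conclusion assumes that the app follows the content in Section 11; if the working questionnaire already names both cues, only the protocol text needs correcting. The primary outcomes and the randomised comparison are not affected. The point is worth acting on because the remedy is cheap before launch, while a missing item cannot be added to data already collected.

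**What to change.** Before launch, add two named options to the 3-hour exposure checklist: one for having drunk alcohol, one for having seen or heard media promoting quitting. Name both in Section 11. Because the end-of-day survey repeats all EMA questions, they carry over without further change. The recoding already planned in Section 14 then gives each cue its own binary variable, and no alcohol-adjusted model is required. If the sponsor prefers not to add the items, remove the two cues from Aim 2 so that the aim matches what is measured. Adding them costs two checklist options in the app and a few seconds per survey, with no extra staff or visits.

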***Pilot study*** I have conducted a pilot study (first in Asia) to examine the feasibility of using low-intensity EMA for documenting smoking cues and smoking-related behaviors (See additional materials). In total, 302 smokers installed the EMA app (designed by the primary investigator) in their own smartphone for a 2-day data collection and contributed 1,744 EMA (48% of all EMA prompts) and 693 valid EMA pairs for further analysis. The completion rate of 4+ and 6+ EMA pairs in the overall participants was 29.1% and 13.2%, respectively. Findings showed that exposure to tobacco point-of-sale (POS) displays (odds ratio [OR]=19.55,  $p<.01$ ) and health warnings (OR=14.27,  $p<0.02$ ) were significantly associated with subsequent purchase of tobacco, consistent with other EMA observational studies. Exposure to the POS displays apparently led to subsequent craving (OR=1.57) and tobacco consumption (OR=1.47), but the sample size was not sufficient to show statistical significance. Findings were presented in the International Symposium on Digital Health 2019 (20).

During Jan 2020 to Oct 2020, I conducted another pilot study using EMA to investigate exposure to alcohol advertisements and alcohol drinking culture in university students. Participants completed 5 regularly prompted EMA surveys with an EMA app in their smartphone every day for 14 consecutive days. The results showed that the 48 participants responded in 2474 EMA (73.5% of all EMA prompts). The compliance rate of 49+ (70%) and 56+ (80%) EMA was 70.8% and 45.8%, respectively.

These two pilot studies suggests several improvements to increase the EMA compliance: (1) Complicated steps to set up an EMA schedule with the EMA app increase participants' burden in real-world participation. Future app development should reduce these complicated steps and use a more user-friendly interface. A simpler set-up procedure can also save recruitment time for each participant in the outdoor environment, as their available time for recruitment is limited. (2) To sustain a higher EMA compliance for time-based system-triggered EMA, separate assessments (in the alcohol EMA pilot study) is more preferred than pair-based assessments (in the tobacco pilot

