#### **14. Statistical analysis**

Intention-to-treat approach will be used to include all consented participants in the analysis and assume non-respondents at the 3-month follow-up as smokers. Chi-squared and t-tests will be used to compare sociodemographic and smoking characteristics of participants to assess the balance between intervention and control group.

The primary comparison is the prevalence of tobacco abstinence and the score of IBC-S between the EMA-based smoking intervention group and the control group. Logistic regression model and linear regression will be used to compare the 7-day PPA and the score of IBC-S between intervention and control group at 3 months, respectively. We will also use multiple logistic regression and multiple linear regression adjusted for imbalance socio-demographic smoking characteristics assessed at baseline to account for imbalances in baseline characteristics.

We will transfer checklist options of smoking cues to binary outcomes. For example, an EMA question asked 'In the past 3 hours, have you been exposed to (check all that apply)' followed by these checklist options: family smoking; friends smoking; partner smoking; receive tobacco products from others; receive encourage of smoking from others). We will recode response into a series of dichotomous variables. Generalized estimating equation analysis will be used to examine the causal relationship between smoking cues and smoking-related behaviors in all participants. A linear mixed model will be used for the association analysis when the outcome is not binary.

Direct operating costs will include app development, salary (of nurses and research assistants), recruitment, telephone follow-up, and publicity items. Costs for study design, analysis, report

writing, and irrelevant administration will be excluded. The cost per successfully recruiting a smoker to participate will be calculated by dividing the total cost by the number of smokers who have joined. Similarly, cost per participant who use smoking cessation aids and per quitter at 3-month follow-up will be calculated.

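### As worded, the 3-hourly EMA puts tobacco purchase and consumption in one yes/no entry; purchase should be a separate item and consumption recorded as a number

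*Protocol*

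**What the plan says.** Section 2 (Aims) names three behaviours for the observational aim: "Smoking-related behaviors include purchase of tobacco, tobacco consumption, and nicotine craving".

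Section 11 (Smartphone application) numbers the behaviours recorded in each time-based EMA. Craving has its own entry. Purchase and use share the next one: "whether he/she has bought/consumed tobacco (traditional cigarettes, heated tobacco products and electronic cigarettes) in the past 3 hours (yes/no". The section describes no other purchase item. The end-of-day (EoD) survey adds the day's total consumption and repeats the EMA questions.

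Section 8 gives an example of the schedule, with prompts 3 hours apart: "he will be asked to complete an EMA survey at 9:00 am, 12:00 nn, 3:00 pm, 6:00 pm and an EoD survey at 9:00 pm". Section 7 requires "daily consumption of tobacco products (including traditional cigarettes, electronic cigarettes, and heated tobacco products) in the past week" and sets no minimum or expected amount per day.

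In the pilot reported in section 4, exposure to point-of-sale (POS) displays (OR 19.55) and to health warnings (OR 14.27) "were significantly associated with subsequent purchase of tobacco, consistent with other EMA observational studies". Consumption was reported separately: "Exposure to the POS displays apparently led to subsequent craving (OR=1.57) and tobacco consumption (OR=1.47". Section 14 plans the analysis: "Generalized estimating equation analysis will be used to examine the causal relationship between smoking cues and smoking-related behaviors in all participants", with a linear mixed model for outcomes that are not binary.

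**The concern.** There are two linked problems, and both are fixed at data collection.

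- **Merging.** A single yes to bought-or-consumed does not show which of the two happened. Consumption is presumably much commoner than purchase in daily smokers, so most yes answers would reflect consumption and purchase would be hidden. No later analysis plan can separate the answers. The pilot's clearest result, the one for purchase, could then not be estimated again from this item.
- **Dichotomising.** Even as its own question, any consumption in 3 hours is a coarse measure for people who use tobacco every day. The more a person smokes, the more often the answer is yes whatever the cue, and a cue that raises use from one to three cigarettes in a window leaves the answer unchanged. The amount is asked once a day and cannot be tied to a cue reported in one window.

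**Working it through.** The protocol states no amount smoked, no expected share of yes windows and no purchase frequency, so there is no figure to reproduce. The calculations below show ranges under stated assumptions.

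**1. Dilution if the item is single**

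From the documents: purchase OR 19.55 (section 4), used only to illustrate size.

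Assumed: baseline purchase probability per window p0 = 1%, 5% or 10%; consumption in a share c = 60% or 85% of windows, independent of purchase and of the cue.

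- Purchase probability with the cue: p1 = 19.55·p0 / (1 − p0 + 19.55·p0), which gives 16.5%, 50.7% and 68.5%.
- Probability of yes on the merged item: 1 − (1 − c)(1 − p), with p = p0 or p1.
- Example, p0 = 5% and c = 85%: without the cue 1 − 0.15 × 0.95 = 0.857; with it 1 − 0.15 × 0.493 = 0.926. The ratio of the two odds is 2.08.

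| Baseline purchase | Merged OR, c = 60% | Merged OR, c = 85% |
|---|---|---|
| 1% | 1.31 | 1.22 |
| 5% | 2.50 | 2.08 |
| 10% | 3.90 | 3.14 |

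**2. Ceiling if the item is split**

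Assumed: k products per day over 16 waking hours. The mean per 3-hour window is m = 3k/16. With Poisson timing, P(yes) = 1 − exp(−m). Information on the log rate is m for a count and m²·exp(−m)/(1 − exp(−m)) for yes/no, so the share kept is m/(exp(m) − 1).

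| k per day | m | P(yes) | Information kept by yes/no |
|---|---|---|---|
| 2 | 0.375 | 31% | 82% |
| 5 | 0.9375 | 61% | 60% |
| 10 | 1.875 | 85% | 34% |
| 15 | 2.8125 | 94% | 18% |
| 20 | 3.75 | 98% | 9% |

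**3. Sensitivity of P(yes)**

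- A waking day of 15 or 17 hours at k = 10 gives 86% or 83%.
- Even spacing, min(1, 3k/16), gives 38% at k = 2, 94% at k = 5, and 100% from about k = 5.3.
- If smokers vary around a mean of 10 per day (gamma, shape 2 to 4), the average is 73% to 79%.
- A 90% share of yes needs about 12 per day under Poisson timing and about 5 per day under even spacing.

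**The case against.** **The slash may be shorthand.** Section 11 summarises the questionnaire. It also writes family, friends and partner smoking with slashes, and section 14 lists those as separate checklist options recoded to separate binary variables. The next two behaviour entries in section 11 ask the reasons for consumption alone, which suggests that consumption is identified on its own. This stands: a reader might infer that the app certainly asks one merged question, and the text does not prove that. But the recoding in section 14 is described for cue checklists, and the purchase and consumption entry is marked yes/no and unpacked nowhere. The ambiguity about a named Aim 2 outcome remains.

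**The ceiling may be mild.** A reader might infer that the answer is yes in nearly every window. The documents do not support that: any daily user can enter, including e-cigarette users, and no amount is given. At 2 per day the Poisson figure is 31%.

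**POS cues are asked daily.** POS display, health-warning and hotspot exposure appear among the EoD questions, next to daily consumption, so exposure and amount share a time scale. This stands. It limits the argument for a count per window chiefly to the mood and social cues asked at each prompt.

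**The study is larger than the pilot.** It schedules 440 × 28 = 12,320 time-based prompts. At the pilots' response rates of 48% and 73.5% that is about 5,900 to 9,100 answers, so even at 94% yes some 350 to 540 no windows remain. A reader might infer that a ceiling explains the pilot's non-significant consumption result. The protocol attributes that result to sample size ("tobacco consumption (OR=1.47), but the sample size was not sufficient to show statistical significance") and gives nothing to show another cause.

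**Other momentary measures exist.** Each EMA also records craving and asks whether consumption was due to a cue. These help, but neither gives purchase or amount.

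**Conclusion.** The point holds as a cheap improvement limited to the observational Aim 2. The randomised primary outcomes (IBC-S and validated abstinence) are untouched.

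What the documents establish is that one entry, as worded, covers two outcomes that Aim 2 and the pilot keep apart, with no other purchase item described. If it is asked that way, the loss is permanent and large: in the illustration an odds ratio of 19.55 falls to between 1.22 and 3.90. That range rests on assumed purchase and consumption frequencies and on their independence.

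The ceiling is a risk whose size depends on the amount smoked. Across 2 to 20 per day, yes/no keeps between 82% and 9% of the information in a count, assuming Poisson timing, 16 waking hours and accurate reporting. The loss is small for light users and large from about 10 per day upwards.

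**What to change.** In section 11, state two separate items for each time-based EMA:

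- (a) bought tobacco in the past 3 hours, yes/no;
- (b) number consumed in the past 3 hours, recorded by product type.

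In section 14, analyse (a) with the planned GEE in logistic form and (b) with a log-link count GEE, keeping any-versus-none consumption as a supporting analysis. Name the count model explicitly, because section 14 would otherwise send a non-binary outcome to a linear mixed model, which suits small counts with many zeros poorly.

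The cost is about one extra tap in a survey planned to take about a minute, and some rounding in reported counts. E-cigarettes have no common unit with cigarettes or heated sticks, so yes/no can be kept for them. If the app already asks two questions, one clarifying sentence settles the merging issue, and only the count remains to be considered.
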